### 2.4. Sample Size

The sample size calculation will be based on the minimum sample size formula for mean comparison. Considering data from a similar study conducted in other healthcare settings [6] and assuming a minimal detectable mean difference of 0.52 and a variance of 1.64 (“number of attempts” variable), a minimum sample size of 95 participants was obtained. Accounting for a 20% loss rate, the required sample size increases to 114 participants, with 57 in each group.

For the sample size required for arterial puncture, the calculation will follow data from a study by Grandpiere et al. [3], which reported a 34% difference in success rates using ultrasound compared to the traditional technique. To demonstrate a minimum difference of 37% in the first-attempt success rates between the two groups, with an alpha error of 0.5%, 90% power, and accounting for a 20% loss rate, the required sample size is 80 participants, with 40 in each group.

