## Abstract

**Background**: Vascular access in emergency departments (ED) is challenging for patients with difficult venous access (DIVA), causing delays and discomfort. Ultrasound-guided techniques may offer improved outcomes, making it crucial to assess their benefits, risks, and the effectiveness of validated identification systems. **Objectives**: To contribute new evidence regarding the effectiveness of validated tools for identifying DIVA and to assess the clinical benefits of ultrasound-guided vascular access in emergency care, and to assess their utility in arterial puncture for arterial blood gas sampling, from now on ABG, within the ED. **Methods**: This study follows the Standard Protocol Items: Recommendations for Interventional Trials (SPIRIT) guidelines for protocol development and the Consolidated Standards of Reporting Trials (CONSORT) guidelines for the conduct and reporting of the randomized clinical trial (RCT). The trial will be conducted in Spain throughout 2025. The study population will consist of 114 subjects with difficult intravenous access (DIVA), identified using the DIVA scale for individuals under 14 years of age and the A-DICAVE scale for adults, along with 80 subjects from the general surgical area (GSA). Participants will be randomly assigned, in a 1:1 ratio, to either the Control Group (CG) (traditional technique) or the Experimental Group (EG) (ultrasound-guided technique). Data collected will include sociodemographic characteristics, procedure-related variables (e.g., time required, human resources, and materials used), as well as pain levels, assessed using validated scales (EVA, FLACC, PAINAD), and overall satisfaction from both patients and healthcare professionals. Ethical approval has been obtained, and the trial will be registered as an RCT through an official clinical trial registry before recruitment begins. **Results**: Expected results suggest ultrasound guidance will significantly improve first-attempt success rates, reduce procedural time, enhance patient comfort, and optimize resource utilization compared to traditional techniques. **Conclusions**: The integration of ultrasound-guided vascular access into routine emergency protocols could enhance patient safety, satisfaction, and procedural efficiency in emergency care settings.

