### 2.6. Statistical Methods

The data will be analyzed using SPSS software, version 22. Initially, normality tests will be performed to assess the distribution, homogeneity, and comparability of the sample, employing kurtosis, skewness coefficients, and the Shapiro–Wilk test. A descriptive analysis will then be conducted using measures of central tendency and dispersion (SD) for quantitative variables, alongside calculations of the median and interquartile range (IQR). Qualitative variables will be expressed as frequencies (n) and percentages (%).

Subsequently, appropriate statistical tests will be conducted to determine whether the hypothesis can be rejected, analyzing relationships between the different variables. For qualitative variables, the Chi-square test will be used, or Fisher’s exact test if values < 5 are observed in the sample. For quantitative variables, Student’s t-test will be applied, or the Mann–Whitney U test in cases where the data do not follow a normal distribution.

In all calculations performed in the study, an alpha error of 0.05 and a beta error of 0.2 will be considered, with a 95% confidence level.

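### The venous-access sample size of 95 is a per-group number used as the trial total, so power is about 58% without losses and 48% after the planned 20% loss, not 80%

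*Protocol article*

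**What the plan says.** Section 2.4 of the protocol article sizes the peripheral venous (PIVC) comparison on the number of puncture attempts. The method is named: "The sample size calculation will be based on the minimum sample size formula for mean comparison". The inputs are given as "assuming a minimal detectable mean difference of 0.52 and a variance of 1.64", and the result is that "a minimum sample size of 95 participants was obtained". After a 20% loss allowance, "the required sample size increases to 114 participants, with 57 in each group". The abstract repeats 114 as the whole DIVA population, randomised 1:1.

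The PIVC paragraph states no error rates of its own. Section 2.6 supplies them for all calculations in the study: "an alpha error of 0.05 and a beta error of 0.2 will be considered, with a 95% confidence level".

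**The concern.** The usual formula for comparing two means returns the number of patients in each group. With the plan's inputs it returns almost exactly 95, but the plan carries 95 forward as the number for both groups together. The PIVC comparison would then have about half the patients that its own assumptions require.

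Number of attempts is the variable the protocol chose for sizing this part of the trial. If power is near one half, a real effect of the planned size would be missed about as often as it is found. Readers who rely on the stated beta of 0.2 would nevertheless take a null result as reasonably strong evidence against that effect.

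**Working it through.** **Inputs.** Difference 0.52 and variance 1.64 (SD = √1.64 = 1.281), section 2.4. Alpha 0.05 and beta 0.2, section 2.6. Allocation 1:1, section 2.5. Loss 20%, section 2.4. Two assumptions are mine: the test is two-sided (sidedness is not stated), and 1.64 is the common within-group variance.

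**Reproducing the plan's 95.**

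n per group = 2 × (z₀.₉₇₅ + z₀.₈₀)² × variance / difference²
= 2 × (1.960 + 0.842)² × 1.64 / 0.52²
= 95.2

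The 95 is therefore reproduced, but per group. The total is 2 × 95.2 = 190.4, or 192 when each group is rounded up to 96.

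**Other settings, with 1:1 allocation.**

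| Reading | Per group | Total |
|---|---|---|
| Two-sided 0.05, 80% power | 96 (95.2) | 192 |
| One-sided 0.05, 80% | 75 | 150 |
| Two-sided 0.05, 90% | 128 | 256 |
| One-sided 0.05, 90% | 104 | 208 |
| 1.64 read as an SD, two-sided, 80% | 157 | 314 |
| 1.64 read as an SD, one-sided, 80% | 123 | 246 |

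None of these gives a total of 95. One further reading does, and it is taken up under the objection.

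**Power of the planned size** for 0.52 attempts, SD 1.281, two-sided 0.05 (noncentral t):

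| Evaluable per group | Where it comes from | Power | Difference detectable with 80% power |
|---|---|---|---|
| 57 | 114 randomised, no loss | 57.5% | 0.68 |
| 47.5 | 95 in total | 49.9% | 0.74 |
| 45.6 | 114 less 20% | 48.3% | 0.76 |
| 96 | what the inputs require | 79.9% | 0.52 |

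Beta is thus about 0.43 without loss and 0.52 after it.

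**Loss allowance.** The plan's 114 is 95 × 1.20. But 114 × 0.80 = 91.2, so even the stated 95 is not preserved. The correct inflation is 95 / 0.80 = 118.75, or 119. Applied to 95 or 96 per group, it gives 119 or 120 per group, which is 238 to 240 in total.

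**The case against.** The best defence is that 1.64 might be the sum of the two groups' variances, as it would enter an unequal-variance form of the formula. Then n = (1.960 + 0.842)² × 1.64 / 0.52² = 47.6 per group, or 95.2 in total, which is the plan's figure used as the plan uses it. On that reading 57 per group has about 86% power, and 45.6 per group after losses about 77%, so the main defect disappears. It cannot be excluded, because the study from which the inputs were taken is not at hand. The wording does not support it, however: section 2.4 gives "a variance of 1.64 (“number of attempts” variable"), a single variance of a single variable. If it is what was meant, section 2.4 still needs correcting, because its inputs as printed do not lead to its total.

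Three smaller objections have some force.

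- **Error rates.** They come from section 2.6, and the arterial calculation in section 2.4 departs from them, so that sentence does not govern everything. But the PIVC paragraph gives no other rates, and these are the ones that return 95.
- **Sidedness.** It is not stated. One-sided power would be about 61% to 70%, still short of 80%.
- **Role of the outcome.** The article does not formally name a primary outcome, so a null result on attempts need not decide the trial. It is nonetheless the outcome on which the size was justified.

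The loss allowance is a separate and minor error, worth 5 patients on the plan's own total (119 against 114).

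**Conclusion.** The concern holds on the plain wording of the protocol. The stated inputs require 95 to 96 evaluable patients per group, and the plan randomises 57 per group. Power for 0.52 attempts is 57.5% with no loss and about 48% after the planned 20% loss, against the 80% implied by section 2.6. With losses allowed for, 114 is a little under half of the 238 to 240 needed.

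This rests on a two-sided test and on 1.64 being the common variance within a group. One-sided testing does not rescue the size. Only reading 1.64 as the sum of the two variances would, and the text does not say that. The statement must be corrected before the sample size can be relied on.

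**What to change.** 1. In section 2.4, state what 1.64 denotes, give the alpha, sidedness and power used for the PIVC calculation, and say that 95 is the number per group.
2. Compute the loss allowance as n / (1 − 0.20).
3. Then choose one of two courses:
   - **Keep 80% power for 0.52 attempts:** plan about 119 to 120 per group, 238 to 240 in total, and change the abstract to match.
   - **Keep 114:** state that 57 per group gives about 58% power for 0.52 attempts (about 48% after 20% loss), and that 80% power is reached only for a difference of about 0.68 (no loss) to 0.76 (after loss). Qualify section 2.6 so that beta 0.2 is not claimed for this comparison.
4. If the sponsor confirms from its source that 1.64 is a sum of two variances, say so and show the formula. The total of 95 then stands, and only the loss allowance needs changing (119 instead of 114, or 120 for equal groups).

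Keeping 114 costs only rewording of sections 2.4 and 2.6 and a less favourable power statement. Extra patients, about 124 to 126 (238 − 114 to 240 − 114), are needed only if the sponsor wants 80% power for 0.52 attempts.

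### The arterial-puncture sample size is stated at alpha 0.5% and 90% power, which contradicts the study-wide alpha 0.05 and beta 0.2; 80 patients fits alpha 5%, and the planned 37 points exceeds the cited 34 without explanation

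*Protocol article*

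**What the plan says.** Section 2.4 (Sample Size) bases the arterial calculation on a published study "which reported a 34% difference in success rates using ultrasound compared to the traditional technique". It then sets its own target: "To demonstrate a minimum difference of 37% in the first-attempt success rates between the two groups". The error rates and result follow: "with an alpha error of 0.5%, 90% power, and accounting for a 20% loss rate, the required sample size is 80 participants", split as 40 per group. It gives no success rate for either group and does not say whether the test is one- or two-sided.

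Section 2.6 (Statistical Methods) states: "In all calculations performed in the study, an alpha error of 0.05 and a beta error of 0.2 will be considered", together with a 95% confidence level. For categorical outcomes it names the chi-square test, with Fisher's exact test when counts are small.

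**The concern.** The two sections give different error rates for the same comparison: alpha 0.005 against 0.05, and beta 0.10 (90% power) against 0.20. The wording of section 2.6 makes no exception for the arterial part. An arterial result of p = 0.02 would count as significant under section 2.6 but not at the level used to size the comparison in section 2.4. A threshold should not be open to choice once data are in hand.

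The second question is whether 80 patients follows from the inputs printed beside it. If alpha really is 0.5%, the comparison may have much less power than the stated 90%. If it is not, a wrong figure has been published.

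Third, a difference called a minimum is larger than the difference reported by the study the calculation is said to follow. A larger planned difference makes the same number of patients look better powered.

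**Working it through.** **Inputs from section 2.4:** difference 37 points (source: 34), alpha 0.005, power 0.90, loss 20%, 40 per group. **From section 2.6:** alpha 0.05, beta 0.2, chi-square test. **Assumptions:** two-sided test; control success rate 30-55%, because the document gives none. Rates outside that range are checked in step 4.

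**1. Reproducing 80.** The unpooled formula for two proportions is

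n per group = (z_alpha/2 + z_power)² × (p1q1 + p2q2) / d².

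With d = 0.37 the requirement is largest at 31.5% vs 68.5%, where p1q1 + p2q2 = 0.4316 and d² = 0.1369.

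- Alpha 0.05, power 90%: (1.960 + 1.282)² = 10.51; 10.51 × 0.4316 / 0.1369 = 33.1 per group. Multiplied by 1.2 this is 39.7, i.e. 40 per group and 80 in total. The plan's figure is reproduced.
- Alpha 0.005, power 90%: (2.807 + 1.282)² = 16.72; 16.72 × 0.4316 / 0.1369 = 52.7 per group before loss. At 50% vs 87% it is 44.3. Both already exceed 40.

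The pooled-variance formula, which matches the chi-square test, needs 35-59 evaluable per group at alpha 0.005 over all possible control rates. With the factor 1.2 the smallest total is 84, so this formula never gives 80.

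**2. Power for 37 points.** This is exact binomial enumeration of the two-sided Pearson chi-square test. A 20% loss leaves 40 × 0.8 = 32 per group.

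| Alpha | Evaluable per group | Power, control rate 30-55% |
|---|---|---|
| 0.005 | 32 | 55-75% |
| 0.005 | 40 | 71-87% |
| 0.05 | 32 | 88-95% |

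**3. Power for the source's 34 points, 32 per group.** 82-89% at alpha 0.05; 45-61% at alpha 0.005.

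**4. Where the shortfall at alpha 0.005 disappears (37 points).**

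- With all 40 per group analysed: 91% at 5% vs 42%, 91% at 58% vs 95%, and 95% at 60% vs 97%.
- With 32 per group: 85% at 60% vs 97%, 91% at 62% vs 99%, and 95% at 63% vs 100%.
- At 60% vs 97% the unpooled formula with alpha 0.005 gives 32.9 per group; × 1.2 = 39.4, i.e. 40.

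So 90% power at alpha 0.005 needs success rates close to floor or ceiling in one group.

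**The case against.** The strongest reply is that section 2.6 governs the analysis and gives alpha 0.05 with 95% confidence, while 0.5% appears once, in a sample-size sentence, and looks like a slip for 5%. On that reading the comparison is not badly underpowered; one figure is wrong. This largely stands, and the reconstruction in step 1 supports it. It does not remove the contradiction on the page, and correcting the alpha still leaves 90% power against beta 0.2. That second conflict does not itself reduce power, since a design sized for 90% also meets an 80% requirement, but the document still states two targets.

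A reader might infer that 40 per group cannot deliver 90% power at alpha 0.5%, or that 80 arises only from alpha 0.05. The document supports neither. It gives no success rates, and step 4 shows that extreme rates reach 90% and that the unpooled formula can return 40 per group at alpha 0.005. The match at alpha 0.05 is also conditional: it relies on near-worst-case rates, the unpooled formula and a loss factor of 1.2.

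A reader might also infer that the 37 points misquotes the 34. Section 2.4 describes the 34 as a difference in success rates and the 37 as a difference in first-attempt success, so they may be different measures. A target difference need not equal a published estimate. What stands is that the gap is unexplained.

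The loss factor of 1.2 leaves 32 per group instead of 33. That is one patient per group and immaterial.

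**Conclusion.** The contradiction between sections 2.4 and 2.6 on alpha and on power is literal and needs no assumption. The printed alpha of 0.5% does not fit 80 patients at mid-range success rates: power after loss is about 55-75%, not 90%, if the control rate is 30-55% and the test is a two-sided chi-square. Alpha 5% does fit, with 88-95% after loss, so a slip is the likely explanation. The document alone does not prove it, because the success rates and sidedness are unstated. The step from 34 to 37 points is unexplained; at alpha 0.05 it is worth about six percentage points of power across the assumed range (88-95% against 82-89%). This should be corrected before analysis because it concerns the decision threshold and costs little.

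**What to change.** - Use one two-sided alpha of 0.05 and one power in both section 2.4 and section 2.6.
- State the control and ultrasound first-attempt success rates assumed for arterial puncture.
- Justify the 37-point difference, including whether it measures the same thing as the cited 34, or plan on 34.
- Restate the power that 80 patients give after 20% loss, computed from the protocol's own rates. The 82-89% for 34 points illustrates a control rate of 30-55% and should not be copied in as the plan's figure.

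The cost is rewording and a stated power that may be slightly less favourable. No extra patients are needed if the common power is the 80% of section 2.6. Keeping 90% as the target for 34 points could require more, since the pooled formula at alpha 0.05 then needs up to 44 evaluable per group.

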### 2.5. Randomization of the Sample

Random assignment of participants to the Control Group (CG) and the Experimental Group (EG) will be conducted with a 1:1 ratio using a simple randomization method. Each participant will have an equal probability of being assigned to either group, minimizing bias and ensuring the equitable distribution of characteristics between the groups. To achieve this, a computer-generated random number sequence will be used. Additionally, random permuted blocks will be created to reduce the predictability of the random sequence, while ensuring an equal number of subjects in each group.

Those responsible for carrying out the techniques shall be unaware of the randomization code so that their performance is not constrained.

Details of the sample selection, inclusion criteria applied, and methods used for random assignments to CG and EG will be documented. This will ensure participants’ right to withdraw their data and guarantee the transparency and replicability of the study.

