## 1. Introduction

Approximately 90% of patients who attend emergency departments (EDs) require venipuncture, with short peripheral intravenous catheters (PIVCs) being the most commonly used invasive devices in these settings [1]. Despite its routine nature, vascular access can be particularly challenging in a subset of patients, even for experienced healthcare professionals. When two or more attempts are required to achieve successful cannulation, patients are typically classified as having difficult intravenous access (DIVA) [2]. Repeated failed attempts are associated with damage to venous and arterial structures, increased pain and distress for the patient, delays in diagnosis and treatment, and greater consumption of healthcare resources [3,4]. Several studies have examined the clinical and demographic factors associated with DIVA. Conditions such as obesity, hypotension, generalized edema, advanced age, and the presence of multiple hematomas have been frequently cited as risk factors for cannulation failure [5,6]. Among adult populations, the prevalence of DIVA has been estimated to range between 10% and 24% [1]. In pediatric settings, the prevalence is even higher, with reports indicating that approximately 37% of children may fall into this category [7].

To address the challenges of early identification, a number of clinical tools and scoring systems have been developed. The first of these, the DIVA scale, was validated by Yen et al. for use in pediatric populations and aimed to guide clinical decision making from the point of triage [8]. This approach was later expanded by Kuensting et al., who incorporated additional variables such as the patient’s clinical history, the anticipated treatment plan, and the skill level of the staff performing the procedure [9].

In adult populations, the A-DIVA scale, introduced by van Loon et al. in 2016, provided a framework for identifying patients at risk of difficult venous access in surgical settings [10]. More recently, Salleras et al. developed the A-DICAVE scale, a simplified and ED-appropriate tool designed to support early recognition of DIVA and promote the use of ultrasound-guided techniques in these cases [11,12].

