### 2.1. Scope of the Study

The study will be carried out in the ED of the Hospital Nuestra Señora de Sonsoles (HNSS) de Ávila, belonging to the Regional Health Management of Castilla y León, Spain. This center has a catchment area of 158,140 inhabitants [26], which are spread over a total of 469 localities [27].

This population has an average age of 47.99 years with a dependency ratio of 42.56% for those under 65 and 63.20% for the total population. The population over 65 years of age constitutes 26.08% of the total population [26].

The HNSS ED receives about 47,000 emergencies per year (about 5000 pediatric patients), a figure that is increasing year after year. Some 34 nurses work in the ED in morning/evening/night shifts. The number of nurses per day is 6/7/5, respectively [28]. The nurses in the service have the official nationally recognized qualification, and therefore the necessary competences to perform vascular punctures. Prior to the study proposal, 99% were trained in the use of ultrasound-guided puncture by in-house training provided by nurses from the department who had acquired their skills and experience externally through regulated training.

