### 2.2. Design

The RCT will collect data derived from the procedures performed on patients selected through probabilistic random sampling. The study workflow is outlined in the following flowchart (Figure 1). Following the CONSORT criteria, after an initial identification of the possible participants in the study, the inclusion and exclusion criteria will be applied, in order to subsequently assign each subject to the relevant group depending on the technique to be performed (PIVC or arterial punctures). Once the technique has been selected, using a randomized system, the subjects will be assigned to the Control or Experimental Groups, and the technique will be performed using the relevant procedure, using the traditional technique for CG and an ultrasound-guided technique for SG. After obtaining the required number of samples, the data obtained shall be analyzed.

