### 2.3. Participants

The study will recruit DIVA patients identified using the A-DICAVE scale for patients aged > 14 years and the DIVA scale for those aged < 14 years, who attend the ED and require short PIVC or AGB.

Inclusion criteria:Prescription for CIP or GA cannulation.Informed consent signed by the patient or patient’s representative.A score ≥ 3 on the A-DICAVE scale or ≥4 on the DIVA scale for PIVC.

Exclusion criteria:Scores below 3 on the A-DICAVE scale or below 4 on the DIVA scale for PIVC.Inability to obtain informed consent from the patient or patient’s representative.

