### 3.1. Measurement Instruments

To identify DIVA patients during PIVC catheterization, two scales will be used depending on the patient’s age:

For patients aged ≥14 years, the A-DICAVE scale [11] will be applied. This scale consists of three items: vein visualization (scored 0–2), vein palpation (scored 0–2), and a history of puncture difficulty (scored 0–1). The total score is categorized as follows: easy (0–2 points) and difficult (3–5 points).

For patients aged <14 years, the DIVA4 scale [2] will be used. This scale, scored 0–10, includes four items: visible vein after tourniquet application (0–2 points), palpable vein after tourniquet application (0–2 points), age (≥3 years: 0 points; 1–2 years: 1 point; <1 year: 3 points), and history of prematurity with gestational age < 38 weeks (0–3 points). It has been demonstrated that scores > 4 typically indicate the need for multiple punctures to achieve adequate venous access.

In order to assess the level of satisfaction of professionals, patients and their families, an ad hoc instrument will be used, based on a 5-point Likert scale, ranging from 1 = “not at all satisfied” to 5 = “very satisfied”. Each item will be rated with a value from 1 to 5. To determine the general level of satisfaction, the following ranges of interpretation have been established:Not at all satisfied.Not very satisfied.Satisfied.Quite satisfied.Very satisfied.

To assess the satisfaction levels of professionals, patients, and their families, a 5-point Likert satisfaction scale will be applied. If patients are unable to express their satisfaction, only the response from their family members will be recorded.

Pain assessment will utilize numerical scales (0–10):○For adults and children aged > 7 years, the Visual Analogue Scale (VAS) [30] will be used.○For children aged < 5 years, the FLACC scale (Face, Legs, Activity, Cry, Consolability) [31] will be applied.○For adults with cognitive impairments, the PAINAD scale (Pain Assessment in Advanced Dementia) [32] will be employed.

Once the corresponding technique has been carried out, the data from the measuring instruments will be recorded through the form that will have the necessary items for their evaluation, together with the rest of the variables, as shown in Table 2.

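### Section 2.5 credits unstratified allocation with ensuring equitable characteristics, which it cannot do; an age-group stratum in the venous (PIVC) comparison would be a near-free improvement

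*Protocol article*

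**What the plan says.** Section 2.5 (Randomization of the Sample) states that assignment "will be conducted with a 1:1 ratio using a simple randomization method". It credits the equal allocation probability with "minimizing bias and ensuring the equitable distribution of characteristics between the groups". It then adds that "random permuted blocks will be created to reduce the predictability of the random sequence", with equal group sizes as a further aim. No stratification factor is named.

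Section 2.2 (Design) sorts patients into PIVC or arterial puncture before allocation: "Once the technique has been selected, using a randomized system, the subjects will be assigned to the Control or Experimental Groups". Technique is the only separation described.

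Section 2.3 (Participants) shows that the venous cohort joins two entry routes, with patients "identified using the A-DICAVE scale for patients aged > 14 years and the DIVA scale for those aged < 14 years" and a different cut-off on each scale. Section 3.1 repeats the split: "For patients aged <14 years, the DIVA4 scale [2] will be used".

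Section 2.4 sets the venous cohort at 114, with 57 per arm, from a difference of 0.52 attempts and a variance of 1.64. Section 2.6 names the chi-square or Fisher test and the t-test or Mann-Whitney test, all unadjusted comparisons of two groups. Table 2 lists age among the recorded variables.

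**The concern.** The sentence in section 2.5 claims a property that the method does not have. Equal allocation probability makes the arms alike on average over repeated trials. In one trial of 114 patients it leaves chance differences. Blocks do not change this for characteristics, because they constrain only the number allocated to each arm.

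Age group is a natural factor to examine because the protocol itself divides the venous cohort at 14 years. Scale and entry cut-off change there, the Introduction quotes different prevalences of difficult access for children and adults, and the youngest children have their own pain instrument. Yet age group appears neither in the allocation nor in the tests that the article names.

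Two things are at stake. A chance excess of children in one arm would move the unadjusted difference in attempts if children and adults differ in attempts. Any variation between the age groups would also stay in the error term, although a variable known before allocation could remove it.

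**Working it through.** The plan gives no imbalance probability, so there is no figure of its own to reproduce. The 57 per arm and the variance of 1.64 are taken as printed.

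**Step 1. Share of children (assumption).** The documents do not state it. Two proxies can be built from their figures.

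- Raw attendance (section 2.1): "about 47,000 emergencies per year (about 5000 pediatric patients". 5,000 / 47,000 = 10.6%; 0.106 x 114 = 12-13 children.
- Attendance weighted by prevalence of difficult access. The Introduction says that "approximately 37% of children may fall into this category" and gives 10-24% for adults. Children: 5,000 x 0.37 = 1,850. Adults: 42,000 x 0.10 = 4,200, up to 42,000 x 0.24 = 10,080. Share: 1,850 / (1,850 + 10,080) = 15.5%, up to 1,850 / (1,850 + 4,200) = 30.6%. Times 114: about 18 to 35 children.

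The second proxy suits the PIVC cohort better, because only patients with a difficult score enter it. It still assumes that children and adults need a PIVC, and consent, at equal rates, and that the quoted prevalences carry over to the entry scores.

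**Step 2. Chance of a gap of at least 10 percentage points in children, either direction.** Section 2.5 names both simple randomisation and blocks, so both were computed.

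*Blocks (57 against 57).* With m children, the number in one arm is hypergeometric (114 patients, m children, 57 drawn). A 10-point gap is 0.10 x 57 = 5.7 children. The difference in counts has the same parity as m, so it must reach 6 if m is even and 7 if m is odd. That is why the probability zigzags.

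*Simple randomisation.* The same probability is averaged over arm sizes distributed as Binomial(114, 0.5). Holding both arms at 57 here would be wrong, because the arm sizes vary too.

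| Children m | Share | Blocks | Simple |
|---|---|---|---|
| 12 | 10.5% | 0.124 | 0.086 |
| 13 | 11.4% | 0.074 | 0.099 |
| 18 | 15.8% | 0.198 | 0.140 |
| 19 | 16.7% | 0.130 | 0.150 |
| 26 | 22.8% | 0.264 | 0.212 |
| 34 | 29.8% | 0.306 | 0.245 |
| 35 | 30.7% | 0.223 | 0.250 |

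Over every count from 18 to 35, the range is 13-31% with blocks and 14-25% with simple randomisation. At 12-13 children it is about 7-12%.

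**Step 3. Effect on the difference in attempts.** Shift = imbalance x gap in mean attempts between children and adults. The documents give no such gap; 0.5 to 1.0 is assumed.

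- Shift: 0.10 x 0.5 = 0.05, up to 0.10 x 1.0 = 0.10 attempts, which is 10-19% of the target of 0.52.
- Standard error of the difference: sqrt(1.64 x 2 / 57) = 0.24.
- Shift in standard errors: 0.05 / 0.24 = 0.2, up to 0.10 / 0.24 = 0.4.

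**Step 4. Variance that an age stratum would remove.** Share = p(1 - p)d² / 1.64, with p the child share and d the assumed gap.

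- Lowest: 0.155 x 0.845 x 0.25 / 1.64 = 2%.
- Highest: 0.306 x 0.694 x 1.0 / 1.64 = 13%.

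**The case against.** The strongest reply is that unstratified 1:1 allocation is a valid design for 114 patients at one centre. Chance imbalance is not bias, and the test's error rate already allows for it. Choice of strata and covariates is often left to a full protocol or analysis plan, which is not shown. On this view only one word, the claim to ensure balance, needs changing. The reply is right about validity, and the absence of strata would not be a fault in itself. But the article does positively assert a balance that the method cannot give, and it names only unadjusted tests.

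A second reply is that the probabilities rest on a child share that the documents do not state. That stands. The figures are conditional on Step 1, and the raw attendance share gives clearly lower ones.

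A third is that the consequence is small: at most about 0.4 standard errors, on an assumed gap. That also stands.

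A reader might go further and infer that an imbalance in children could not be told apart from an ultrasound effect unless allocation is stratified. The documents do not support this: age is recorded (Table 2), and adjusting the analysis would deal with it. A reader might also infer that age group is the most influential factor. No section ranks the factors. The Introduction lists obesity, hypotension, edema, advanced age and hematomas as risk factors, and entry by difficulty score may narrow any age gap in attempts.

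**Conclusion.** The point holds as a misstatement in section 2.5 together with a missed, inexpensive improvement. It does not show an invalid design or a biased comparison. Under the prevalence-weighted child share, the kind of imbalance that the sentence says is prevented has a chance of roughly one in eight to one in three. Under the raw attendance share the chance is about one in fourteen to one in eight. The consequence for the attempts outcome is modest, and both the shift and the variance gain rest on an assumed gap between children and adults. Age and scale are known before allocation, so the improvement is worth making even at this size.

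**What to change.** 1. Within PIVC, use separate permuted-block lists for patients under 14 and patients aged 14 or over. This is the cut in section 3.1; section 2.3 leaves patients aged exactly 14 unassigned and should be aligned with it. Arterial puncture is already separated before allocation in section 2.2.
2. Include that age group in the PIVC analysis, as a model term or through a stratified rank test.
3. If recruitment has begun, leave the allocation as it is and make the analysis change only.
4. In section 2.5, replace the claim of ensured equitable characteristics with a statement that randomisation balances characteristics in expectation, and that closer balance is sought only on the stratification factors.

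Cost: one more computer-generated list, one model term and one rewritten sentence. No extra patients or measurements are needed.
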